### Study procedure

Between 2023 and 2026, all adult patients with XDP fulfilling the inclusion criteria for MRgFUS pallidothalamic tractotomy will be invited to participate in the study. The patient’s written, informed consent will be secured on hospital admission for the procedure.

The procedure will be performed by one of the investigators ([name]) inside the MR imaging (MRI) suite, using a 1.5 Tesla MRI system (GE Optima MR450, USA) and the ExAblate Neuro device (InSightec, Haifa, Israel) to deliver the focused ultrasound. The patient’s head will be shaved and immobilized using a stereotactic frame under local anesthesia. An elastic diaphragm will be attached to the patient’s head and connected to the ultrasound transducer, and the patient will be positioned inside the bore of the MRI. A reference MRI scan will be performed to position the transducer to the target, after which the MRI images (T1-weighted axial and T2-weighted axial/coronal MRI at 1 mm slices) will be fused to the preoperative CT scan for the skull-correction algorithm. Stereotactic treatment planning will then be performed to target the PTT. It is usually located at the midcommisural line (0 to 1.0 mm posterior) in the anterior-posterior direction, 8–10 mm lateral to the intercommisural line in the mediolateral direction, 0-1.5 mm inferior to the intercommisural line in the dorsoventral direction, and 6.5–7.5 mm to the thalamo-ventricular border [18]. The lesion will be made 3 mm lateral to the mamillo-thalamic tract and superior and medial to the medial subthalamic nucleus [16, 19, 20]. Once the target is set, a series of low-power sonications producing temperatures between 40-45^o^C and lasting 10–20 seconds will be performed. Clinical assessment for improvement and treatment side effects will be made after each sonication, and definitive non-reversible thermal ablation will be performed only at the setting wherein the patient experiences tremor reduction or suppression or improvement of the dystonia with no adverse effects. The final sonication temperature usually ranges between 55-63^o^C. After the treatment, the stereotactic frame will be removed and the patient will be monitored in the hospital overnight.

The patients will be assessed within 24 hours of treatment then asked to follow up with the movement disorder neurologist ([name]) at 2 weeks, 3 months, 6 months, 9 months, and 12 months post-treatment through a clinic visit. A written and standardized video protocol for the movement exam will be presented to all participants which will show the rating scales such as XDP-MDSP Scale, BFMDRS, and Movement Disorder Society-Unified Parkinson’s disease Rating Scale (MDS-UPDRS). Video recording will be taken at the initial visit and at each of the follow-up visits. Another blinded assessor, who is not connected with the PGH, will be asked to score the videos of the patients. The primary outcome will be assessed using the XDP-MDSP Scale, BFMDRS, and MDS-UPDRS at each visit, which will then be compared to the pre-treatment baseline recordings. In addition, XDP clinical and functional stage will be assessed [1]. Adverse effects, including skin burn, headache, arm or leg pain, muscle weakness, paresthesia, and unsteady gait, will be monitored at every follow-up.

For patients who have previously undergone a unilateral MRgFUS pallidothalamic tractotomy, the contralateral lesion will be performed at 12 months following the first procedure, provided that there are no serious adverse effects from the first PTT lesioning.

Moreover, we will also look into the: (a) demographic and clinical profile, (b) neuroimaging findings (cranial computed tomography and MRI), (c) MRgFUS treatment parameters (number of sonications, maximum energy, maximum temperature, duration of treatment), (d) change in the non-motor features using the XDP-MDSP Scale, (e) change in the XDP clinical and functional stage, (f) change in the BFMDRS and the part III of the MDS-UPDRS, (g) to determine the improvement in the patient’s quality of life using the five-level EuroQol five-dimensional questionnaire (EQ-5D-5L) at baseline, 3 months, 6 months, 9 months, and 12 months, (h) Montreal Cognitive Assessment (MoCA) (English, Pilipino, or Hiligaynon versions) at baseline, 6 months, and 12 months, and (i) to determine the safety of unilateral and staged bilateral MRgFUS procedure (see supplementary material 2).

The XDP-MDSP scale is a 5-part rating validated rating scale designed specifically for XDP patients [21]. The authors will also utilize the BFMDRS movement scale and disability scale to measure dystonia severity [25] and part-III of the MDS-UPDRS will be used to measure parkinsonism severity [26]. This will be done so that the results can be compared with other literature on the treatment of XDP. The EQ-5D-5L (looking at mobility, self care, usual activities, pain/ discomfort, and anxiety/ depression as well as an overall assessment of their health on a scale from 0–100), will look at the patient’s health at the present time [27]. Meanwhile, the MoCA will be utilized to measure general cognitive functioning. We will be utilizing the English, Filipino, or the Hiligaynon versions, depending on the preference of the patient [28–30].

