### Sample size

The sample size for this study was computed to range between 28 and 70 participants (see Table 1), with an expectation of a medium or large effect, using repeated measures Analysis of Variance (RM-ANOVA) for within-subject comparisons (as measures are taken 3 times per patient). To compute for the sample, the wp.rmanova function from WebPower package was used [24].

**Table 1 Tab1:** Sample Size Computations

F value	Minimum Sample (n*)	Inflated Sample Formula: n* / (1-DOR)
0.25 (Medium Effect)	62.5	69.5
0.30	43.5	48.5
0.35	32.5	36
0.40 (Large Effect)	24.5	27.5

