### Data analysis plan

Descriptive statistics (mean, median, mode) of the numerical and nominal data will be obtained. Parametric tests will be used when our data follow normal distribution, otherwise, nonparametric test (Kruskal-Wallis test) will be used to compare the groups. The means of the 2 observer-masked scores pre-operative, 2 weeks, 3 months, 6 months, 9 months, and 12 months will be compared using a one-way analysis of covariance. A paired t-test will be done for the secondary endpoints: MoCA, EQ-5D-5L, and the nonmotor portion of the XDP-MDSP Scale. P-values of < 0.05 will be considered statistically significant. An interim analysis will be performed at either the 6-month timepoint or when 50% of patients have been enrolled, whichever comes first.

Protocol registration and technical review approval

This protocol was registered in the ClinicalTrials.gov website (Trial registration number: NCT05592028). It has received technical review board approval from the Department of Neurosciences, College of Medicine and Philippine General Hospital, University of the Philippines Manila.

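### Three scales are primary at every visit with no deciding scale, time point or success rule, and two of them also appear as additional outcomes

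*Protocol article*

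**What the plan says.** All of this is in the protocol article.

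- **Study procedure, primary outcome.** "The primary outcome will be assessed using the XDP-MDSP Scale, BFMDRS, and MDS-UPDRS at each visit". These ratings are to be set against the recordings made before treatment. Follow-up is "at 2 weeks, 3 months, 6 months, 9 months, and 12 months post-treatment through a clinic visit", which makes five scheduled visits.
- **Study procedure, additional outcomes.** Item (f) of the list of further things to be examined is "change in the BFMDRS and the part III of the MDS-UPDRS". The later paragraph describing the scales brings in BFMDRS (movement and disability) and MDS-UPDRS part III so that results can be set against other published work, which is a supporting role.
- **Data analysis plan.** The masked scores, pre-operative and at the follow-up visits up to "12 months will be compared using a one-way analysis of covariance". The secondary list is separate: "A paired t-test will be done for the secondary endpoints: MoCA, EQ-5D-5L, and the nonmotor portion of the XDP-MDSP Scale". The threshold is "P-values of < 0.05 will be considered statistically significant", with no adjustment for several scales or visits.
- **Sample size.** The calculation uses a repeated-measures ANOVA, "as measures are taken 3 times per patient".

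**The concern.** A primary endpoint should tell the reader in advance which result decides the trial. Here three scales hold that status at each of five visits, and nothing says whether one, two or all of them must improve, or when. A favourable scale could be put forward as the primary result after the data are seen. That raises the false-positive rate and biases the reported effect upwards. All participants are treated, so no concurrent control group tempers a selected result.

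Separately, a reader cannot tell whether the trial has one primary scale or three. BFMDRS and MDS-UPDRS are primary in one sentence, additional in the next list, supporting in the description of the scales, and absent from the secondary endpoints. The primary sentence also does not restrict MDS-UPDRS to part III, whereas the later text does.

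**Working it through.** The article states no family-wise error rate, so there is no figure of its own to reproduce. It gives only the per-test threshold of 0.05.

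**Inputs from the article:** 3 scales; 5 scheduled follow-up visits; 0.05 per test; one across-time comparison of the masked scores. The assessment within 24 hours of treatment is not counted, because the article does not say that the scales are rated then.

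**Assumptions, not in the article:** two-sided tests; significance on any one scale counts as efficacy; the across-time comparison is run once per scale; the correlations shown below.

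**Formula for k independent tests:** chance of at least one false positive = 1 - (1 - 0.05)^k.

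**Reading A: one across-time test per scale (Data analysis plan), k = 3**
- Independent: 1 - 0.95^3 = 1 - 0.857 = 14.3%.
- Three correlated tests, 200,000 multivariate-normal simulations: 13.6%, 12.5% and 10.9% at between-scale correlations of 0.3, 0.5 and 0.7.
- Check with three repeated-measures F tests (28 patients, six time points, between-visit correlation 0.6, 6,000 simulated trials): 13.9%, 14.2%, 12.3% and 10.8% at between-scale correlations of 0, 0.3, 0.5 and 0.7.

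**Reading B: every scale at every visit tested against baseline, k = 3 × 5 = 15**
- Independent, either direction: 1 - 0.95^15 = 53.7%.
- Independent, false improvement only (0.025 per test): 1 - 0.975^15 = 31.6%.
- Correlated, by simulation:

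| Correlation between scales / visits | Either direction | Improvement only |
|---|---|---|
| 0.3 / 0.5 | 44.0% | 23.1% |
| 0.5 / 0.7 | 34.1% | 17.2% |
| 0.7 / 0.7 | 29.8% | 14.9% |
| 0.7 / 0.8 | 25.8% | 12.9% |
| 0.8 / 0.9 | 18.9% | 9.5% |

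**After correction**
- One primary scale with one test: 5%.
- Three primary scales at 0.05/3 = 0.0167 each: at most 5%; if independent, 1 - (1 - 0.0167)^3 = 4.9%.

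**Double listing.** A scale that appears in two lists is still one set of measurements and one test. It adds nothing to k.

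The interim analysis in the Data analysis plan has no stated allocation of alpha. It could add to these figures and is not included in them.

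**The case against.** The strongest counter-argument is that the article does not plan 15 tests. The Data analysis plan describes one comparison across all time points, and the Sample size section is built on a repeated-measures ANOVA. The Study procedure section says that visits will be compared with baseline but assigns no test to each visit. This stands, and it makes Reading A the better account of the written plan.

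A reader might therefore infer too much by concluding that each of 15 primary comparisons is judged at 0.05 and that the chance of a false efficacy finding is some 30-50%. The documents do not support that. It needs separate visit tests that the Data analysis plan does not describe and correlations that the article does not give. It also counts false worsening as efficacy.

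Three further objections stand in part.

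- No passage says that one significant scale is enough, and the stated objective is to estimate efficacy. The any-scale rule is an assumption, but nothing in the text excludes it.
- The paragraph on the scales suggests that BFMDRS and MDS-UPDRS part III were meant as supporting measures. If so, the primary-outcome sentence is wrong as written, and the secondary list still omits both.
- An unseen full protocol or analysis plan might say more. That does not settle the matter: the article does state the primary outcome, and its statement conflicts with its own lists.

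The across-time test is also not a complete answer. It shows neither the direction nor the visit of a change, so the promised comparison with baseline would need further contrasts, for which no adjustment is stated.

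**Conclusion.** The point holds as a defect of endpoint definition with a moderate effect on error control. Three scales are primary with no lead scale, decisive time point or success rule, at an unadjusted 0.05, and the status of two of them is contradictory.

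If any one scale suffices, the two-sided false-positive rate is about 11-14% under the analysis as written, more than double the nominal 5%. The figure of about 54% is an upper limit that needs 15 separate, independent tests counted in either direction. Under the correlations tried it is about 19-44%. For false improvement only, it is about 15-32%, from independence down to correlations of 0.3-0.7 between scales and 0.5-0.7 between visits.

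Confidence is high in the contradiction and in the lack of a deciding endpoint. It is lower in any single error figure, because the success rule, sidedness and correlations are all assumed. It would be wrong to infer that the duplicate listing inflates the error rate; it is a contradiction of status only.

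**What to change.** 1. Name one primary endpoint, for example change from baseline to month 12 in the XDP-MDSP score, tested at two-sided 0.05. It is the disease-specific scale, and the earlier four-patient experience cited in the Introduction reports it at 6 months and 1 year. State which of its five parts count, because the nonmotor portion is already a secondary endpoint.
2. Test BFMDRS movement and then MDS-UPDRS part III, both at month 12, in fixed sequence as key secondary endpoints.
3. Report all other visits as estimates with 95% confidence intervals, without claims of significance.
4. If all three scales must stay primary, prespecify one test per scale at 0.05/3.
5. Reconcile the primary-outcome sentence, item (f) and the description of the scales in Study procedure with the secondary list in the Data analysis plan.
6. Align the planned analysis of covariance and the sample-size basis (repeated-measures ANOVA, three measurements) with the chosen endpoint.

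**Cost.** This is more than a change of wording, because the analysis and sample-size text must be revised. BFMDRS and MDS-UPDRS lose stand-alone primary status, and under the fixed sequence they can be claimed formally only if the tests before them succeed. Month 12 and the order of the scales are one reasonable choice; another would serve if it is fixed in advance and controls the error.

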### Withdrawal criteria

No clinical withdrawal criteria will be set, but participants may withdraw from the study at any point if they decide not to participate any more. Their data will be included if they were able to complete at least 1 follow up, with the last observation carried forward.

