## Introduction

X-linked dystonia-parkinsonism (XDP) is an uncommon and progressive neurodegenerative movement disorder which presents with adult-onset parkinsonism and dystonia [1]. It is also found almost exclusively in males from Panay Island in the Philippines and all the cases described so far have been linked to Filipino ancestry [1]. XDP is linked to mutations in the DYT3/TAF1 gene [2]. The prevalence of XDP globally is 5.74 per 100,000 individuals in Panay Island and 0.31 per 100,000 in the Philippines [1]. The majority of patients (95%) are males, and the mean age of onset is 39–40 years [1, 3]. Furthermore, the mean duration of illness is approximately 16 years and the mean age of death is approximately 55.6 years [1].

XDP is characterized by focal dystonic movements affecting the upper and lower extremities, the craniofacial area, and neck and shoulders, before becoming generalized within two to five years [1]. In some cases, parkinsonism may present initially [3]. Dystonia may co-exist or is replaced by parkinsonism usually beyond the tenth year of illness, manifesting as tremors and other symptoms, such as bradykinesia and gait instability [1]. As a result, patients have decreased life expectancy and poor quality of life [1, 4].

Pharmacologic treatment includes oral medications (carbidopa/levodopa, trihexyphenidyl, biperiden, haloperidol, diazepam, zolpidem, milacemide, anticonvulsants, and antihistamines). However, the response rate is variable and, in several cases, suboptimal [5, 6]. Chemodenervation using botulinum toxin A and muscle afferent blockade have been also been utilized [7, 8].

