### Setting and participants

The study will be conducted at the PGH, Manila, Philippines. Adult XDP patients aged between 18–65 will be recruited for this study. All participants will undergo MRgFUS pallidothalamic tractotomy. Based on the list of patients as of December 2022, there are approximately 30 XDP patients who have sought consult at the PGH within the past 4 years.

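### Last observation carried forward lets a 2-week score stand for month 12 in a progressive, uncontrolled setting; the bias depends on why patients leave, and uncertainty is understated

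*Protocol article*

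**What the plan says.** Under Withdrawal criteria, the protocol article sets no clinical grounds for withdrawal; "participants may withdraw from the study at any point if they decide not to participate any more". For those who leave, it states: "Their data will be included if they were able to complete at least 1 follow up, with the last observation carried forward".

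Four other places bear on how that rule works:

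- Study procedure schedules follow-up "at 2 weeks, 3 months, 6 months, 9 months, and 12 months post-treatment through a clinic visit", after an assessment within 24 hours of treatment.
- Study procedure also says the motor scales are scored at each visit, "which will then be compared to the pre-treatment baseline recordings".
- Setting and participants describes a single arm: "All participants will undergo MRgFUS pallidothalamic tractotomy".
- The Introduction describes the disease as "an uncommon and progressive neurodegenerative movement disorder". It also reports a four-patient series treated in Taiwan, with 30–36% improvement on the XDP-MDSP Scale at 6 months and 1 year.

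The Data analysis plan section compares visit means by analysis of covariance and states no adjustment for imputed scores.

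**The concern.** Carrying the last score forward assumes that nothing changes after the patient is last seen. That is a strong assumption for a disease described as progressive, followed for a year after a single lesion. A patient who leaves after the 2-week visit is given that score at months 3, 6, 9 and 12. There is no control arm in which the same error would arise and partly cancel, so any distortion passes straight into the change from baseline.

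Two things are at stake. The later-visit estimate may be wrong by an amount that the analysis cannot reveal. Also, a carried score is counted as a measured one, so the analysis claims more information about later visits than was collected. Separately, withdrawn patients with no follow-up are left out altogether.

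**Working it through.** **Implied dropout.** Table 1 inflates n\* by n\*/(1 − DOR) without giving DOR. Solving DOR = 1 − n\*/inflated n for each row:

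| Effect size | n\* | Inflated (stated) | Implied DOR | n\*/0.9 |
|---|---|---|---|---|
| 0.25 | 62.5 | 69.5 | 10.1% | 69.4 |
| 0.30 | 43.5 | 48.5 | 10.3% | 48.3 |
| 0.35 | 32.5 | 36 | 9.7% | 36.1 |
| 0.40 | 24.5 | 27.5 | 10.9% | 27.2 |

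A single rate of 10% reproduces all four rows to within rounding. It is used below as the planners' implied figure.

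**Bias of the month-12 mean.** Bias = d × (carried improvement − true month-12 improvement), where d is the fraction withdrawn. The carried improvement is assumed to be 30–36%, borrowed from the four-patient series because the article gives no 2-week value. All withdrawals are assumed to occur after at least one follow-up. With d = 0.10:

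| Assumed true month-12 improvement in those who left | Bias, percentage points |
|---|---|
| Same as carried | 0 |
| 15% | 0.10 × 15 = 1.5 to 0.10 × 21 = 2.1 |
| 0% (benefit wholly lost) | 0.10 × 30 = 3.0 to 0.10 × 36 = 3.6 |
| −10% (worse than baseline) | 0.10 × 40 = 4.0 to 0.10 × 46 = 4.6 |

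In the third row, with completers also at 30–36%, the reported mean stays at 30–36% while the true mean is 27.0–32.4%. The bias is proportional to d.

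**Direction when departure depends on the early result.** Assume an early gain of 33 points, SD 25 at both times, correlation 0.6, and that the 10% with the poorest early result leave. The mean of the lowest tenth of a standard normal distribution is −1.755. Hence

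bias = 0.10 × [(33 − true month-12 mean) − 25 × (1 − 0.6) × 1.755] = 0.10 × [(33 − true month-12 mean) − 17.55].

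| True month-12 mean | Bias, random withdrawal | Bias, early non-responders leave |
|---|---|---|
| 33 (stable) | 0 | −1.8 |
| 20 | +1.3 | −0.5 |
| 10 | +2.3 | +0.5 |

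Simulation gives the same values. The sign therefore depends on both waning and the reason for leaving.

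**Effect on the test.** Take an extreme case: no true change at month 12, a carried early gain averaging 30 points, SD 30, 10% dropout, and a one-sample t-test of change from baseline at two-sided 5% (sidedness is not stated in the article). Over 20,000 simulated trials, the chance of a significant apparent benefit rises from about 2.5% to 6.9% with 28 patients, 8.1% with 36 and 11.8% with 70.

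**Effect on precision.** Suppose carried scores have the same SD as measured ones. The nominal standard error at month 12 is then √0.9 = 0.949 times the one from measured patients alone, about 5% smaller. The uncertainty about what the missing patients would have scored is left out.

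**The case against.** The strongest reply is that nothing in the article shows benefit fading within a year. The four-patient series reports the same 30–36% range at both 6 months and 1 year. The Introduction describes illness lasting about 16 years, with generalization over two to five, so a large fall within 12 months is not implied. At the implied dropout the bias is also small against a 30–36% effect. All of this stands, and it is why the direction is stated as conditional. It does not rescue the method: four patients cannot establish stability, and the understated uncertainty remains even if the bias is nil.

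A second reply is that analysis sets and missing-data sensitivity analyses are usually left to an analysis plan, which is not shown here. That also stands, so no omission is charged. The carry-forward rule itself is stated.

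Three stronger readings are tempting and are not supported:

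- A reader might infer that the rule must favour efficacy. The second table of bias figures shows zero and negative cases, and the article does not say who is likely to leave.
- A reader might infer that it drops early failures. A poor result seen at the 2-week visit stays in, and the poor score is carried forward, which counts against efficacy. Only withdrawn patients with no follow-up are left out, and nothing shows that their outcomes are worse.
- A reader might set the statement that every participant is treated against the one that "definitive non-reversible thermal ablation will be performed only at the setting wherein the patient experiences tremor reduction or suppression or improvement of the dystonia", and infer a contradiction that leaves an enriched set. The second statement reads most naturally as choosing the sonication setting. The withdrawal rule does not remove a patient who was sonicated but not ablated, since that patient has not withdrawn.

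**Conclusion.** The point holds in a limited form. The article fixes a method that lets a 2-week score represent month 12, in a disease it calls progressive and without a control arm. Later benefit is overstated if patients worsen after leaving, unaffected if benefit is stable, and can be understated if early non-responders leave. At about 10% dropout with complete loss of a 30–36% benefit, the overstatement is 3.0 to 3.6 percentage points. That would not by itself create an effect of 30%, but it can raise the false-positive rate where there is no lasting effect. Uncertainty is understated in every case. The effect of leaving out patients with no follow-up cannot be determined from the document.

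The dropout rate is inferred from Table 1. The carried benefit, its loss, the SDs and the correlation are assumptions. Month 12 is used because it is the last compared visit; the article names no single primary time point. The change should be made before any analysis, but the point does not invalidate the trial.

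**What to change.** Replace the carry-forward rule with a linear mixed model for repeated measures, fitted to all observed visits of every treated patient. Visit should be a categorical factor, within-patient correlation should be modelled, and baseline should be included as an outcome. The article does not currently plan such a model, so it must be specified as a new method alongside or in place of the analysis of covariance.

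Report how many treated patients have no follow-up. Those with a baseline score enter the model but say little about month 12, so the model does not recover their outcomes and the count has to be visible.

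Add a sensitivity analysis that sets missing month-12 values to baseline, that is, no benefit. This is also a single imputation. It is meant as a stress test of the mixed model's missing-at-random assumption, not as the main estimate.

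The cost is revised analysis wording, slightly wider intervals and possibly a smaller estimate. No extra visits or measurements are needed.
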